## 2. General Principles of Analysis

- 1) All statistical analyses of the clinical trial results will be based on two-sided testing, with a significance level of 5%.
- 2) The statistical software used for analysis will be SAS® Version 9.4 (SAS Institute Inc., Cary, NC).
- 3) For continuous data, the mean and 95% Confidence Interval will be presented. For categorical data, frequency and percentage (%) will be presented.
- 4) If necessary, a subgroup analysis will be performed by categorizing subjects based on their initial characteristics from the screening or baseline visits.

## 3. Handling of Missing Data

In this study, missing values will be imputed using the Last Observation Carried Forward (LOCF) method. This imputation will only be applied to efficacy endpoints in the FAS.

## 4. Analysis of Demographic and Baseline Data

Descriptive statistics for demographic characteristics and pre-treatment subject characteristics will be presented for each group. For continuous variables, the mean and confidence interval will be presented, and an independent t-test will be performed. For categorical variables, frequency and proportion will be presented, and a Chi-square test or Fisher's exact test will be performed.

### • Statistical Analysis of Outcome Measures

1. Primary Outcome Measures: Change in WURSS-21-K Total Score (Symptom Score + Quality of Life Score) from Baseline to Day 7
  - Research Hypothesis: The change in the WURSS-21-K total score from baseline to Day 7 in the test group is not equal to the change in the WURSS-21-K total score from baseline to Day 7 in the control group.
  - The primary outcome measures will be analyzed using an ANCOVA model, with the groups as a fixed effect and the baseline WURSS-21-K total score as a covariate. If necessary, variables that show a statistical difference in demographic characteristics or variables that may affect cold symptoms can be included as covariates. The least-square mean (LSM) for the difference between the test group and the control group will be calculated, and the 95% confidence interval and p-value for this difference will be presented.

## 2. Secondary Outcome Measures

- 1) The changes in the following secondary outcome measures from baseline to Day 7 will be tested using the same method as the primary efficacy endpoint: Nasal Congestion Severity Score, Nasal Symptom Score VAS, Systemic Symptom Score VAS, WURSS-21-K symptom score, WURSS-21-K quality of life score, and EQ-5D-5L score. Additionally, the pre- and post-treatment differences within each group will be analyzed using a Student's paired t-test, depending on the normality of the data.
- 2) To compare the differences in trends between the groups, Repeated Measures Analysis of Variance (RM ANOVA) will be used, with Dunnett's procedure for multiple comparisons (comparing each time point against baseline).
- 3) The Global Evaluation of Efficacy satisfaction and cold recovery status at Day 7 will be analyzed using the Chi-square test. However, if the Global Evaluation of Efficacy satisfaction score is treated as a continuous variable, an Independent t-test or Wilcoxon rank-sum test will be performed.

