|                         | 
 
7. Duration of common cold symptoms
 
8. Common cold recovery status on Day 7
 
9. Global Evaluation of Efficacy score on Day 7
 
10. Change in the EQ-5D-5L score from Baseline to Day 7
 
 
• Exploratory Outcome Measures
 
 
1. Change in the WURSS-21-K total score according to the common cold pattern identification (Wind-Cold type, Wind-Heat type, or Other types).
 
                                                                                                                                                                                                                                                                                                                                                                                                                                                                                                                                                                                                                                                                                                                                                                                                                                                                                                                                                                                                                                                                                                                                                                                                                                                                                                                                                                                                                   |

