#### 2) Rationale

This clinical trial is designed to evaluate the efficacy and safety of GGTCS for patients with nasal congestion due to the common cold. The primary outcome measure is the WRUSS-21-K. The change in the WRUSS-21-K from baseline to Day 7 (after a total of 21 doses, 3 times a day for 7 days) will be compared between the test group (GGTCS) and the control group (placebo).

The hypothesis for this clinical trial is as follows:

[Hypothesis]  $H_0$ (Null Hypothesis):  $\mu_t = \mu_c$  vs.  $H_1$ (Alternative Hypothesis):  $\mu_t \neq \mu_c$

$\mu_t$  : The mean change in the WRUSS-21-K score from baseline to Day 7 in the test group.

$\mu_c$  : The mean change in the WRUSS-21-K score from baseline to Day 7 in the control group.

Table 1. Change in WRUSS-21-K of Eungyo-san, Sams0-eum, placebo between pre- and post-treatment.

|                   | Pre-Treatment | Post-Treatment | Change (Before-After)* |
|-------------------|---------------|----------------|------------------------|
| Eungyo-san (n=44) | 56.28(30.47)  | 13.86(22.43)   | 44.00(22.27)           |
| Sams0-eum (n=42)  | 54.74(30.98)  | 17.05(24.29)   | 40.12(18.78)           |
| Placebo (n=42)    | 66.48(31.64)  | 33.33(30.02)   | 29.09(21.89)           |

\*: Change adjusting WRUSS-21-K score of baseline.

Previous studies (K.-I. Kim, M. Hong) showed that the mean (standard deviation) change in the WRUSS-21-K score from pre- to post-treatment was 29.09 (21.89) for the placebo group, 44.00 (22.27) for the Eungyo-san treatment group, and 40.12 (18.78) for the Samso-eum treatment group. The mean difference in effect was 14.91 for the Eungyo-san treatment group compared with the placebo group, with a pooled standard deviation of 22.09. The mean difference in effect for Samso-eum compared with the placebo group was 11.03, with a pooled standard deviation of 20.39. In this clinical trial, the significance level ( $\alpha$ ) was set at a two-sided 5%, and the power ( $1-\beta$ ) is 80%. Based on the results of the previous studies, the effect difference is set at 10 and the standard deviation at 21. The calculated number of subjects required to confirm the effect of the GGTCS group compared with the placebo group is as follows.

$$\left\{ \frac{2 \left( z_{1-\frac{\alpha}{2}} + z_{\beta} \right)^2 * \sigma^2}{|\mu_T - \mu_c|} \right\} = \left\{ \frac{2(1.96 + 0.84)^2 * 21^2}{10^2} \right\} = 69.227 \approx 70$$

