## 4) Assessments of WURSS-21-K, Nasal Symptom Score VAS, Systemic Symptom Score VAS, EQ-5D-5L

## 5) Assignment of Randomization Number

- Subjects who are deemed eligible for this clinical trial based on the inclusion/exclusion criteria will be assigned a randomization number in the following format, in the order of their enrollment.
- Site codes: Daejeon University Daejeon Korean Medicine Hospital 01, Kyung Hee University Korean Medicine Hospital 02, Pusan National University Korean Medicine Hospital 03

|                              |
|------------------------------|
| ✓ KIOM_2024_CC_GGTCS_0X_R000 |
|------------------------------|

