**10.3.2.7.Recovery from Common Cold**

- At Visit 3, cold recovery will be evaluated based on whether all cold symptoms have improved.

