## **11.2. Statistical Analysis of Outcome Measures**

### **11.2.1. Primary Outcome Measures**

Hypothesis: The mean change in the WURSS-21-K total score (symptom score + quality of life score) from baseline to Day 7 is not equal between the test group and the control group.

The analysis will be conducted using an ANCOVA model with the group as the effect and the baseline WURSS-21-K total score as a covariate. If necessary, other variables that show a statistical difference in demographic characteristics or that could affect cold symptoms will also be included as covariates. The least-square mean (LSM) difference between the control and test groups, its 95% confidence interval, and the p-value will be presented.

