### **11.2.2. Secondary Outcome Measures**

- 1) The change from baseline to Day 7 in Nasal Congestion Severity Score, Nasal Symptom Score VAS, Systemic Symptom Score VAS, WURSS-21-K symptom and quality of life scores, EQ-5D-5L score, and duration of cold symptoms will be tested using the same method as the primary outcome measures.
- 2) To compare the differences in trend changes between groups, a Repeated Measures Analysis of Variance (RM ANOVA) will be used, with Dunnett's procedure for multiple comparison correction (comparing each time point to baseline).
- 3) The Global Evaluation of Efficacy satisfaction and cold recovery status on Day 7 will be analyzed using a Chi-square test. If the Global Evaluation of Efficacy score is treated as a continuous variable, an Independent t-test or Wilcoxon rank sum test will be performed.

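### Day 7 recovery is compared by an unadjusted Chi-square although every subject has a baseline WURSS-21-K total: a valid test, but adjusting for baseline would be a cheap gain in efficiency and consistency

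*Protocol*

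**What the plan says.** The synopsis lists "Common cold recovery status on Day 7" as the eighth of ten secondary efficacy outcomes. Section 10.3.2.7 makes it a judgement at Visit 3: "cold recovery will be evaluated based on whether all cold symptoms have improved". Section 10.3.2.6, on symptom duration, instead asks whether the cold has resolved completely.

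The comparison is fixed in two places and no covariate is named in either. The synopsis, under secondary outcome measures, item 3, reads "The Global Evaluation of Efficacy satisfaction and cold recovery status at Day 7 will be analyzed using the Chi-square test". Section 11.2.2(3) reads "The Global Evaluation of Efficacy satisfaction and cold recovery status on Day 7 will be analyzed using a Chi-square test".

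The primary outcome is handled differently. Section 11.2.1 uses an "ANCOVA model with the group as the effect and the baseline WURSS-21-K total score as a covariate", and Section 11.2.2(1) applies the same method to the Day 7 change scores. The optional extra covariates in Section 11.2.1 belong to that ANCOVA and do not reach recovery. The covariate itself is available, because Section 10.2.2, item 4, schedules "Assessments of WURSS-21-K, Nasal Symptom Score VAS, Systemic Symptom Score VAS, EQ-5D-5L" at Visit 2. Section 6.3 does not stratify randomisation by severity.

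**The concern.** A subject who starts with a worse cold may be less likely to be well a week later. If so, a plain two-by-two test leaves explainable variation in the comparison and loses some power. It also makes no allowance for a chance difference in baseline severity between the arms, whereas the primary ANCOVA does. Recovery is easy to understand and will be read beside the primary result, so it is worth analysing it on the same footing when the covariate is already there.

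**Working it through.** **1. The plan's own figure.** Section 5.3 uses a difference of 10, SD 21, two-sided 5% and 80% power. 2 × (1.96 + 0.84)² × 21² / 10² = 69.1 with rounded normal quantiles. Unrounded quantiles give the stated 69.227, hence 70 per group. 70 / 0.8 = 87.5, hence 88. This reproduces, but it concerns the primary outcome only. No power or rate is stated for recovery.

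**2. How prognostic baseline is in Table 1 (Section 5.3).** The table's change column carries the note "Change adjusting WRUSS-21-K score of baseline", so the slope can be recovered.
- Weighted baseline mean: (44 × 56.28 + 42 × 54.74 + 42 × 66.48) / 128 = 59.12.
- Raw changes: 56.28 − 13.86 = 42.42; 54.74 − 17.05 = 37.69; 66.48 − 33.33 = 33.15.
- Slope of change on baseline = (raw − adjusted) / (arm baseline − 59.12):
  - Eungyo-san: (42.42 − 44.00) / (−2.84) = 0.556
  - Samso-eum: (37.69 − 40.12) / (−4.38) = 0.555
  - Placebo: (33.15 − 29.09) / 7.36 = 0.552
- Slope of end score on baseline: 1 − 0.554 = 0.446.
- Pooled SDs are 31.0 before and 25.7 after treatment, so r = 0.446 × 31.0 / 25.7 = 0.54 (0.47 to 0.61 by arm).

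The agreement of the three slopes is what a common-slope adjustment would produce. It is not three independent estimates.

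**3. Power.** Assumptions not in the documents: recovery means that a latent Day 7 score falls below a threshold; that score has correlation r with baseline; recovery is 40% v 60% or 30% v 50%. The simulation (10,000 runs per cell) compared the Chi-square without continuity correction with the Wald test for group in a logistic regression on group and baseline. Entries are power in %, Chi-square → adjusted.

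| r | 70/arm, 40 v 60 | 70/arm, 30 v 50 | 88/arm, 40 v 60 | 88/arm, 30 v 50 |
|---|---|---|---|---|
| 0 | 66.9 → 66.3 | 68.0 → 68.3 | 76.9 → 75.3 | 79.5 → 78.6 |
| 0.3 | 66.8 → 68.6 | 68.1 → 70.6 | 77.0 → 78.0 | 79.0 → 80.0 |
| 0.45 | 66.8 → 71.6 | 67.2 → 73.3 | 76.5 → 81.1 | 79.0 → 82.5 |
| 0.54 | 67.1 → 75.1 | 68.4 → 76.7 | 78.4 → 84.6 | 78.7 → 85.1 |

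A second simulation used the planned 10-point effect (10 / 25.7 = 0.39 SD), placebo recovery of 30 to 50% and a likelihood-ratio test. At r = 0.54, power was 43–44% against 51–53% at 70 per arm, and 54–55% against 62% at 88 per arm. The absolute power depends on the assumed rates, but the gain is similar.

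**4. Type I error.** With 40% recovery in both arms (15,000 runs per setting), the Chi-square rejected in 4.7 to 5.4% of runs and the adjusted test in 4.4 to 5.2%.

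**5. Chance baseline gaps.** The SD of a gap is 31.0 × √(2/n).
- 88 per arm: 31.0 × 0.151 = 4.7 points, which at slope 0.446 is about 2.1 points of end score.
- 70 per arm: 31.0 × 0.169 = 5.2 points, or about 2.3 points of end score.
- Table 1's gap of 66.48 − 56.28 = 10.2 points is 0.33 SD. A gap at least that large, in either direction, has probability of about 3% at 88 per arm and 5% at 70.
- Given a gap of about 0.33 SD, r = 0.54 and 40% recovery, the spurious difference in recovery is 0.54 × 0.33 × 0.386 = 6.9 percentage points (0.386 is the normal density at the 40% quantile). In null runs with such a gap, the Chi-square rejected in 10.5% (70 per arm) and 14.5% (88 per arm), against 4.8% and 5.1% adjusted.

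**The case against.** A Chi-square on a randomised comparison is a legitimate choice. Recovery is one of ten secondary outcomes, the trial was not sized for it, and an adjusted supportive analysis could sit in an analysis plan that is not at hand. All of that stands, and it is why the point is minor. It remains a comment on a method that the protocol itself fixes twice.

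A reader might infer more in four ways, none of which the documents support.
- *That the Chi-square inflates false positives or lets imbalance pass as a drug effect.* The raised rates in step 5 are conditional on an unusual gap. Averaged over all gaps, they are already inside the 5%. The 10.2-point example is a 3 to 5% event, not a typical one.
- *That the gain is reliably 8 points.* That is near the favourable end. The r of 0.54 is for the total score, from other products, and not for recovery. Two arms in Table 1 have end scores of 13.86 (SD 22.43) and 17.05 (SD 24.29), where the SD exceeds the mean on a scale that cannot go below 0. A normal latent score is therefore rough near the floor, where recovery lies.
- *That the unadjusted test favours the arm with milder colds.* This assumes recovery means resolution. Under the wording of Section 10.3.2.7, improvement may count, and in Table 1 the change increases with baseline (slope about 0.55). The direction could then weaken or reverse.
- *That a conflict between recovery and the primary would be due to adjustment alone.* The two also differ in instrument, in dichotomisation and in timing, since Visit 3 falls on Day 7 to 10.

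**Conclusion.** The unadjusted Chi-square for recovery is valid but makes no use of a covariate that the trial collects from everyone and already relies on for its primary analysis. Adjusting for it is an improvement in efficiency and consistency, not the correction of an error. The expected gain is about 6 to 8 points of power if baseline relates to recovery as strongly as Table 1 implies for the end score, about 1 to 3 points at r = 0.3, and nil or a loss of about 1 to 2 points near r = 0. Protection against chance imbalance usually concerns gaps of about 5 baseline points, or about 2 points of end score. The recovery rates, the latent-score model and the carry-over of r to recovery are all assumptions. Severity: minor.

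**What to change.** In the synopsis (secondary outcome measures, item 3) and in Section 11.2.2(3), make the main analysis of Day 7 recovery a logistic regression on treatment group and baseline WURSS-21-K total. From that model, report the standardised (marginal) difference in recovery proportion with its 95% CI and p-value. This keeps the same easily read quantity as a raw difference in proportions. Retain the counts, percentages and Chi-square as supportive. Settle this before unblinding, so that the choice cannot look data-driven.

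Reconcile Sections 10.3.2.6 and 10.3.2.7 so that it is clear whether recovery means improvement or complete resolution. The model estimates the direction of the baseline effect, so the change of method does not depend on that answer, but the interpretation does.

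Cost: a sentence in each of two places and slightly more analysis work, with no new data, visits or subjects. The only statistical downside is the very small power loss if baseline proves unrelated to recovery.

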## 3. Exploratory Outcome Measures

- The analysis methods for comparing different syndromes will be the same as those for the efficacy outcome measures.

### • Statistical Analysis of Safety Assessment

Safety evaluation will involve an analysis of the frequency of adverse events and serious adverse events suspected to be related to the treatment. Adverse events will be collected through subject reports or investigator observation. The manifested adverse events will be described narratively with a detailed explanation, and the frequencies of adverse events with and without a relationship to the clinical trial intervention will be recorded and presented using descriptive statistics. Additionally, the number of events per visit between groups will be compared using a Fisher's exact test. For each laboratory test variable, a paired t-test will be used to analyze whether there is a difference between the pre- and post-treatment values.

## Schedule Summary

|                                                      |                                 | Visit 1
(Screening  ) | Visit 2
(Baseline) | Visit 3  |
|------------------------------------------------------|---------------------------------|--------------------------------------|-----------------------|----------|
| Visit window                                         |                                 | Day -1~0                             | Day 0                 | Day 7-10 |
| Written Consent                                      |                                 | X                                    |                       |          |
| Demographic Survey                                   |                                 | X                                    |                       |          |
| Medical History                                      |                                 | X                                    |                       |          |
| Physical Exam                                        |                                 | X                                    |                       |          |
| Vital Signs                                          |                                 | X                                    | X                     | X        |
| Physical Measurements                                |                                 | X                                    |                       |          |
| Laboratory Test                          |                                 | X                                    |                       | X        |
| Pregnancy Test                           |                                 | △                                    |                       |          |
| EKG                                                  |                                 | X                                    |                       |          |
| Chest X-ray                                          |                                 | △                                    |                       |          |
| PNS (Paranasal Sinuses) X-ray                        |                                 | △                                    |                       |          |
| Pattern Identification for Common Cold Questionnaire |                                 | X                                    |                       |          |
| Inclusion and Exclusion Criteria Evaluation          |                                 | X                                    |                       |          |
| Random Assignment                                    |                                 |                                      | X                     |          |
| Administration of Investigational Product            |                                 |                                      | Daily                 |          |
| Assessments                                          | Nasal Congestion Severity Score | X                                    | Daily                 |          |
|                                                      |                                 |                                      | X                     | X        |
|                                                      | WURSS-21-K                      |                                      | Daily                 |          |
|                                                      |                                 |                                      | X                     | X        |
|                                                      | Nasal Symptom Score VAS         |                                      | Daily                 |          |
|                                                      |                                 |                                      | X                     | X        |
|                                                      | Systemic Symptom Score VAS      |                                      | Daily                 |          |
|                                                      |                                 |                                      | X                     | X        |
| Duration of Common Cold                              |                                 | Daily                                |                       |          |
|                                                      |                                 |                                      | X                     |          |
| Recovery of Common Cold                              |                                 |                                      |                       | X        |

X: All participants, △: If considered necessary by the investigator

 Screening test should be conducted within one day before Visit 2 and the results of clinical laboratory test should be able to be checked at Visit 2.

 CBC (erythrocyte count, leukocyte count, hemoglobin, and hematocrit); LFT (AST, ALT, BUN, creatinine, and glucose).

 If pregnancy status is uncertain, urine hCG test for pregnancy confirmation following will be conducted, and the result must be negative.

|                                                               |                               |   |   |   |
|---------------------------------------------------------------|-------------------------------|---|---|---|
|                                                               | Global Evaluation of Efficacy |   |   | X |
|                                                               | EQ-5D-5L                      |   | X | X |
| Prescription and Delivery of Assigned Investigational Product |                               |   | X |   |
| Distribution and Instruction for Common Cold Dairy            |                               |   | X |   |
| Compliance Test                                               |                               |   |   | X |
| Common Cold Dairy Check                                       |                               |   |   | X |
| Combined Medication Evaluation                                |                               |   | X | X |
| Dropout Status Check                                          |                               |   | X | X |
| Adverse Reaction Evaluation                                   |                               |   | X | X |
| Instruction for Visit                                         |                               | X | X |   |
| Completion of Trial Check                                     |                               |   |   | X |

